#### Recruitment {15}

Female patients who report at least three episodes of involuntary urine leakage weekly during the preceding 3 months will be recruited. A poster will be posted on the bulletin board to illustrate the study details including the research background, criteria for enrollment, potential benefits of the intervention, and other rights of the participants. Patients who meet the inclusion criteria of the study will be given the information sheet, and researchers of the study will demonstrate the details of the study to the patients. Those who have an interest in joining the study will sign the consent forms.

### Assignment of interventions: allocation

#### Sequence generation {16a}

After confirming the consent, statistical program R will be applied to generate a randomization sequence. The allocation will be carried out by a research assistant who has no role in delivering the intervention and the data analysis. All the participants will be allocated in a 1:1:1 ratio.

#### Concealment mechanism {16b}

A circulating nurse who will not take part in this trial will be able to get access to the online randomization database. The investigator will be informed by the nurse that the participant is in the active control group or intervention group.

#### Implementation {16c}

After signing the informed consent forms, participants will be allocated to one of the study arms according to the sequence. The study group will also be revealed at the same time to the participants and the researchers of the study.

### Assignment of interventions: blinding

#### Who will be blinded {17a}

As the present trial is open-labeled, all the participants will not be blinded due to the major difference between the groups (frequencies of the treatment and whether electromagnetic stimulation will be delivered).

#### Procedure for unblinding if needed {17b}

The study does not include any unblinding procedure as this is an open-labeled trial. How about the outcome assessors? You can still name this study as single-blinded.

#### Plans to promote participant retention and complete follow-up {18b}

Before and during the intervention, participants will be given extensive information related to the importance of electromagnetic and PFMT for UI. Participants are allowed to discontinue at any time point of the study without giving a reason. However, if possible, these participants will also be asked to provide the outcomes of the study at week 5 and follow-up. Questionnaires, bladder diary, and pelvic floor muscle function are routinely applied in urology outpatient and are characterized by efficiency and convenience.

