**Discussion:**

The present trial is designed to investigate the effects of a conjunct physiotherapy program for urinary incontinence in women. We hypothesize that this strategy is more effective than pelvic floor muscle training alone, and high-frequency electromagnetic stimulation will be superior to the low-frequency magnetic stimulation group.

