## Methods: participants, interventions, and outcomes

### Study setting {9}

The three groups are the active control group: PFMT, twice per week for 5 weeks; group 1 (low-frequency magnetic stimulation group): PFMT + electromagnetic stimulation, twice per week for 5 weeks, every two sessions will be separated by at least 48 h; group 2 (high-frequency magnetic stimulation group): PFMT + electromagnetic stimulation, continuous treatment for 10 days. All the patients will also receive a 3-month post-intervention follow-up. The randomization process will be conducted by an online random number generator. The random numbers will be kept in opaque envelopes. Then, a research assistant will allocate the numbers to the participants according to the order of inclusion. The present study cannot blind the practitioner and the participants due to the nature of the interventions. However, the outcome assessor and data analyst will be blinded.

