### Interventions

#### Rationale for the choice of comparators {6b}

The participants in the active control group will receive PFMT, which is recommended as the first-line therapy for UI [7]. Patients with UI are usually informed to do PFMT at home or under supervision by physiotherapists.

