### Outcomes {12}

The primary outcome of the study is the International Consultation on Incontinence Questionnaire–Short Form (ICIQ-SF) [27]. It is a widely used four-item questionnaire with full validation that assesses the voiding frequency, voiding volume, impact on quality of life, and the cause of leakage during the past 4 weeks. The total score of the questionnaire ranges from 0 to 21, with 0–7 representing mild UI, 8–12 representing moderate UI, and 13–21 representing severe UI.

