There are several limitations of the current trial. Firstly, it is difficult to keep the participants blinded to the intervention due to the nature of electromagnetic stimulation and PFMT. The researchers will explain the details of the study carefully and inform the participants about the benefits of different interventions. Secondly, the age of the participants ranges from 18 to 75, which is heterogeneous and UI types should be different. We will consider subgroup analysis that may include different age groups and UI types when conducting the research.

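### The retention message, as worded, promotes electromagnetic therapy to unblinded participants and may avoidably widen the expectation gap between the stimulation arms and control on the self-reported ICIQ-SF

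*Protocol article*

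**What the plan says.** The section on promoting retention and complete follow-up {18b} states that, before and during treatment, "participants will be given extensive information related to the importance of electromagnetic and PFMT for UI". The sentence sets no limit by arm.

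Other sections of the article bear on it:

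- **Blinding.** Section {17a} says "all the participants will not be blinded due to the major difference between the groups". Under Implementation {16c}, the allocation is disclosed to participants and researchers once consent is signed. Study setting {9} adds that practitioners are unblinded too, but that "the outcome assessor and data analyst will be blinded".
- **Control arm.** "The participants in the active control group will receive PFMT, which is recommended as the first-line therapy for UI" (section {6b}). Controls get no stimulation.
- **Primary outcome.** This is the ICIQ-SF: "It is a widely used four-item questionnaire with full validation that assesses the voiding frequency, voiding volume, impact on quality of life" (Outcomes {12}).
- **Open question.** Background {6a} calls it unclear whether adding such treatments to PFMT helps, and Objectives {7} makes this the first aim. The abstract gives the expected direction: "We hypothesize that this strategy is more effective than pelvic floor muscle training alone".
- **Response to the lack of blinding.** The limitations paragraph of the Discussion says that researchers will explain the study and "inform the participants about the benefits of different interventions".
- **Recruitment {15}.** The poster is to set out the potential benefits of the intervention.

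**The concern.** The open label is unavoidable here, and the authors acknowledge it. The content of the message is a separate choice, and it can be changed. It tells participants that electromagnetic treatment matters, while the trial exists to find out whether it adds anything to PFMT. Those in groups 1 and 2 hear that everything they receive is important. Controls, if they hear the same message, learn that something they know they are not getting is important.

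The ICIQ-SF is rated by the participant, so blinding the assessor and the analyst does not protect it. Any extra expectation in the stimulation arms would push the result towards the stated hypothesis, and on this outcome alone it could not be separated from a treatment effect. At stake is the reading of a positive result for stimulation against control.

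**Working it through.** **1. Does the message act differently by arm?** The sentence does not say exactly who is told what, so I take each possible reading in turn.

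| Reading of {18b} | Groups 1 and 2 hear | Controls hear |
|---|---|---|
| All participants get the whole message (the literal reading) | Both of their treatments are important | Their own treatment and one they do not get are important |
| Each arm is told about its own treatment | Both of their treatments are important | Their one treatment is important |
| Only the stimulation arms are addressed | Both of their treatments are important | Nothing |

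Under each reading, only the stimulation arms hear stimulation promoted as part of what they receive. Under the first two readings PFMT is promoted in every arm. That supports expectation in controls, but it does not remove the stimulation part of the contrast. Groups 1 and 2 hear the same thing under every reading, so the schedule comparison is little affected.

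**2. Does another section neutralise it?** The passage in the Discussion on informing participants of benefits follows directly on the admission that blinding is difficult. It offers more information on benefits, and nothing about uncertainty. The recruitment poster also speaks of benefits. None of these sections asks for neutral wording.

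**3. Arm size for the illustration.** The plan has no figure on this point, but its sample size gives the arm size. For the group-by-time interaction in a repeated-measures ANOVA, with k = 3 groups, m = 3 time points, f = 0.125 and N = 132, and assuming a correlation of 0.5 and sphericity (neither is stated):

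- λ = f² × N × m / (1 − ρ) = 0.015625 × 132 × 3 / 0.5 = 12.375
- df = (k − 1)(m − 1) = 4 and (N − k)(m − 1) = 258
- power = 0.808; with dropout, 132 / 0.8 = 165

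Both stated figures (44 per group, 165 in total) reproduce, so 44 and 55 per arm are the sizes to use.

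**4. Illustration only.** Assume no true effect and a total expectation shift of b SD between one stimulation arm and control. For a two-sided 5% z-test with n per arm:

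- SE = √(2/n), which is 0.213 for n = 44 and 0.191 for n = 55
- P(significant) = Φ(b/SE − 1.96) + Φ(−b/SE − 1.96)

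| Assumed b (SD) | 44 per arm | 55 per arm |
|---|---|---|
| 0 | 5.0% | 5.0% |
| 0.1 | 7.6% | 8.2% |
| 0.2 | 15.5% | 18.2% |
| 0.3 | 29.1% | 35.0% |

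Worked line for b = 0.2 and n = 44: b/SE = 0.938, so Φ(−1.022) + Φ(−2.898) = 0.153 + 0.002 = 0.155.

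The values of b are assumptions. The document gives no size for the shift and no means of splitting it between the message and the open label itself. The test is also simpler than the planned GEE over repeated time points.

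**The case against.** - **One condensed sentence.** The full participant materials are not shown, and no sentence says that controls are told stimulation is important. A reader might infer that they are. The text supports this only through the unrestricted word for participants, so it remains an inference. What survives is that the literal wording includes controls and that the narrower readings still leave an imbalance.
- **Controls are also encouraged.** The active control section says that the physiotherapists explain the history and benefits of PFMT, set goals and give feedback, and section {6b} describes PFMT as first-line therapy. The Discussion refers to the benefits of different interventions, which can cover every arm. This stands as mitigation, and the net direction is reasoned, not shown.
- **Expectation would differ anyway.** Participants see their arm. The share of any shift due to this message could be near zero, and nothing in the document contradicts that.
- **Other outcomes help.** Electromyography, pressure measurement, Oxford grading and POP-Q are taken by an assessor who is to be blinded, and the diary's urine output is measured with calibrated cups. This stands as partial corroboration. It does not protect the primary outcome.
- **Dropout.** A reader might also infer that disappointed controls will leave more often. No section supports that. Section {18b} itself asks those who stop to give outcomes at week 5 and at follow-up, and the GEE analysis keeps participants with partial data. I make no claim on dropout.

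**Conclusion.** The point holds as an avoidable risk of added expectation bias in the comparison of stimulation with control on the ICIQ-SF. It rests on four statements in the article: the promotional content in {18b}, the absence of an arm restriction, participants' knowledge of their arm, and a self-reported primary outcome. It is not a matter of missing detail, because the article states the content of the message.

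The size is unknown. A reader might take 15.5% or 29.1% as the trial's false-positive rate. The documents do not support that: those figures follow from assumed total shifts and a simple two-arm test, and they would apply to any open-label trial with a shift of that size. They show only that a modest shift matters at this sample size. The plan describes no pooled comparison of both stimulation arms with control, so none is computed.

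Nor do the documents support saying that the result is biased, or that group 1 against group 2 is compromised. The wording should be changed because the change is cheap and the risk serves no purpose in the design.

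**What to change.** Replace the sentence in {18b}, and bring Recruitment {15} and the limitations paragraph of the Discussion into line, with one neutral script used in the same words in all three arms. It should say that:

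- every arm receives active, recommended training;
- it is not known whether adding stimulation, or changing its schedule, helps;
- completing the week-5 and 3-month assessments matters whatever the arm.

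Limit retention messages to completing assessments and the assigned treatment. Treatments, visits and sample size stay as they are.

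**Cost.** This is a protocol revision, so under section {25} it goes to the ethics committee and the registry and, once approved, to participants, sponsors and investigators. The Trial status section describes recruitment as under way since July 2022, so participants already enrolled will have heard different wording. Record the date of change so that the two periods can be identified, and describe in the trial report what participants were told.

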#### Data management {19}

An electronic case report form (eCRF) will be applied to record the data. Data of included participants will be entered into a web-based system Ennov Clinical® 7.5.720. Participants will be identified using the inclusion number, the first letter of their family name, and their given name. This eCRF will be kept by the coordination site of the study. All the data will be entered twice by two individual research assistants.

#### Confidentiality {27}

The full name of each participant and the identification code will be stored in a document kept by the principal investigator. Only the research team can get access to the key to the document. Participants’ private data will not be reported in the publication.

#### Plans for collection, laboratory evaluation, and storage of biological specimens for genetic or molecular analysis in this trial/future use {33}

No biological specimens will be collected in the trial. Questionnaires and electromyography data will be kept in the hospital’s online system as routine clinical assessment and may be used for future cohort studies.

## Statistical methods

### Statistical methods for primary and secondary outcomes {20a}

The main analysis will follow the intent-to-treat principle with all the randomized patients included. The present study will keep the missing data and will not replace them. Normally distributed variables will be presented as mean (SD) values. Non-normally distributed continuous variables will be reported as medium values with interquartile ranges (25th–75th percentile), and percentages will be used for categorical variables. The Shapiro–Wilk test will be used to examine the normal distribution of the variables.

Baseline demographic data will be reported for all patients randomized to the three groups. These data include patients’ age, education level, employment, annual household income, and medical history (BMI, ever pregnant, cigarette smoking, and diabetes). Baseline data will be evaluated by *χ*
^2^ or Fisher’s exact for categorical variables, analysis of variance (ANOVA) for continuous variables, and the Kruskal–Wallis test for non-parametric variables.

Generalized estimation equation (GEE) models will be applied to analyze primary and secondary outcomes collected at different time points. Considering the potential effects of age, BMI, severity of UI, and other variables on the outcomes, subgroup analysis will be carried out to evaluate whether age (< / ≥  50 years), the severity of UI (ICIQ-SF < </ ≥  13 points), and BMI (< / ≥ 25 kg/m^2^) at baseline could have an impact on the effect of the treatment. In view of the fact that patients may not be able to complete all courses of the treatment due to various reasons during the treatment, we will also conduct per protocol analysis. Patients who have completed the original intervention as described above will be included.

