**Methods/design:**

This is a randomized, controlled clinical trial. We will include 165 patients with urinary incontinence from the outpatient center. Participants who meet the inclusion criteria will be randomly allocated to three groups: the pelvic floor muscle training group (active control group), the low-frequency electromagnetic stimulation group (group 1), and the high-frequency electromagnetic stimulation group (group 2). Both group 1 and group 2 will receive ten sessions of electromagnetic stimulation. Group 1 will be treated twice per week for 5 weeks while group 2 will receive 10 days of continuous treatment. The primary outcome is the change in International Consultation on Incontinence Questionnaire–Short Form cores after the ten sessions of the treatment, while the secondary outcomes include a 3-day bladder diary, pelvic floor muscle function, pelvic organ prolapse quantification, and quality of life assessed by SF-12. All the measurements will be assessed at baseline, after the intervention, and after 3 months of follow-up.

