#### Sample size {14}

The present study intends to apply ICIQ-SF as the primary outcome. After calculation, a sample size of 44 in each group is able to provide 80% power to detect a within-between-group difference measured using ICIQ-SF at three time points, assuming a small effect size (Cohen’s *f*) of 0.125 and a two-sided significance level of 5%. Considering that there is a 20% dropout rate, the study will increase the sample size to 165 in total.

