### Methods for additional analyses (e.g., subgroup analyses) {20b}

No subgroup analysis was planned due to the small sample size of the study.

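### The protocol article both plans and rules out subgroup analyses, so no subgroup result has a defined pre-specified status; the same revision should name baseline ICIQ-SF as a covariate in the primary GEE

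*Protocol article*

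**What the plan says.** Three places in the protocol article speak to subgroups.

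- Statistical methods {20a}: "Considering the potential effects of age, BMI, severity of UI, and other variables on the outcomes, subgroup analysis will be carried out". The sentence goes on to fix three binary factors at baseline: age at 50 years, ICIQ-SF at 13 points and BMI at 25 kg/m².
- Additional analyses {20b}, the section meant for this topic: "No subgroup analysis was planned due to the small sample size of the study".
- Discussion, limitations: "We will consider subgroup analysis that may include different age groups and UI types when conducting the research". UI type is not on the {20a} list, and the age groups have no cut-point here.

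On the main analysis, {20a} says "Generalized estimation equation (GEE) models will be applied to analyze primary and secondary outcomes collected at different time points". Section {20c} repeats the choice of GEE. Neither section names a covariate, and neither says that the model has none. The abstract defines the primary outcome as a change: "The primary outcome is the change in International Consultation on Incontinence Questionnaire–Short Form cores after the ten sessions of the treatment". The Outcomes section names only the ICIQ-SF itself.

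**The concern.** The three statements on subgroups cannot all be true. A subgroup result that is reported could be defended from {20a}, one that is withheld from {20b}, and one on UI type from the Discussion. Participants and practitioners know the allocation, and the primary outcome is a questionnaire that the patient completes. In that setting, a list fixed in advance is one of the few protections against selective emphasis. Section {20b} itself says that the sample is too small for subgroups.

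A second, lesser matter sits in the same sentence of {20a}. It opens from the possible influence of age, BMI and severity on the outcome. Such influence is dealt with by covariate adjustment. Subgroup analysis asks a different question, whether the treatment effect varies, and recovers no precision. Baseline ICIQ-SF is collected in every patient, so leaving it out of the model would forgo precision that costs nothing.

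**Working it through.** **Subgroup statements side by side**

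| Section | Status of subgroups | Factors |
|---|---|---|
| {20a} | will be done | age 50, ICIQ-SF 13, BMI 25 |
| {20b} | none planned | none |
| Discussion | may be considered | age groups, UI type |

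All three are current text. No reading makes {20a} and {20b} agree, and the Discussion matches neither.

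**What a subgroup can show.** Inputs: 44 evaluable patients per arm (Sample size {14}); even splits, which is my assumption. Each stratum then has 44/2 = 22 per arm. With a two-sided 5% t-test and 80% power, the detectable pairwise difference is about 0.60 SD at 44 per arm and 0.86 SD at 22 per arm. For an interaction (the difference between two strata in one pairwise effect), the standard error is SD × √(2/22 + 2/22) = 0.426 SD. The overall contrast has SD × √(2/44) = 0.213 SD, so the standard error doubles. The detectable interaction is about 2.80 × 0.426 = 1.19 SD by the normal approximation. Such tests can only be exploratory.

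**The protocol's own sample size.** The article states "a sample size of 44 in each group is able to provide 80% power" for a within-between comparison at three time points, Cohen's f = 0.125, two-sided 5%. It gives no correlation ρ between time points. With k = 3 groups, m = 3 time points and sphericity:

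- noncentrality λ = f² × N × m / (1 − ρ), df1 = (k − 1)(m − 1) = 4, df2 = (N − k)(m − 1)
- at ρ = 0.5 and N = 132: λ = 0.015625 × 132 × 3 / 0.5 = 12.375, df2 = 258, power 0.808
- at N = 129: power 0.797, so 132 (44 per group) is the smallest N in equal groups
- 132 / (1 − 0.20) = 165, as stated

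Other values of ρ give N = 183 (0.3), 156 (0.4), 105 (0.6) and 81 (0.7). Of the values tried, only 0.5 returns the stated figure.

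**Gain from baseline ICIQ-SF as covariate.** In units of SD², for one follow-up visit:

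- unadjusted change: 2(1 − ρ)
- adjusted for baseline: 1 − ρ²
- relative saving: 1 − (1 − ρ²) / [2(1 − ρ)] = (1 − ρ)/2

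| ρ | Change | Adjusted | Saving | Power of a pairwise contrast that had 80% |
|---|---|---|---|---|
| 0.3 | 1.40 | 0.91 | 35% | 94% |
| 0.5 | 1.00 | 0.75 | 25% | 90% |
| 0.7 | 0.60 | 0.51 | 15% | 86% |

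As a check, 300 simulated trials of 132 patients per value of ρ compared two GEE models: group-by-time with baseline among the outcomes, and post-baseline visits with baseline as covariate. The savings were 39%, 24% and 17% at ρ = 0.3, 0.5 and 0.7, in line with the formula given the small number of runs.

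**The case against.** **The unseen SAP may settle it.** It may list covariates and subgroups, and an article may leave such lists to it. This stands for covariates: silence is not a decision against adjustment. It does not stand for subgroups, because the article itself makes opposite statements, and a further document cannot make both true.

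**The {20a} sentence has a proper purpose.** It continues "subgroup analysis will be carried out to evaluate whether age", severity and BMI alter the treatment effect. That is effect modification, the right use of subgroups. This stands. Only the opening clause is prognostic in wording, and planning subgroups does not exclude covariates. A reader might infer that the protocol chose subgrouping in place of adjustment, or that its primary model is unadjusted. The text supports neither.

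**The variance figure is conditional.** This stands too. A correlation of 0.5 is back-solved from the sample size. It shows what fits that calculation, not how ICIQ-SF scores will behave. The comparator also matters: against an analysis of follow-up scores alone, the saving would run from 9% (ρ = 0.3) to 49% (ρ = 0.7). The pairwise figures illustrate precision and are not the trial's stated power, which is for the three-time-point comparison.

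**A false-positive rate near 45% might be quoted.** Simulation under the null gives it for 18 uncorrected pairwise t-tests (six strata, three pairs of arms) with three independent even splits. The protocol describes no such testing. Three independent interaction tests at 5% would give 1 − 0.95³ = about 14%. The 45% therefore holds only on that unstated procedure and is not part of this point.

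**The data analyst is blinded** according to Study setting. That helps, but it does not say which subgroups were planned.

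**Conclusion.** The contradiction is certain and needs no assumption: {20a}, {20b} and the Discussion give three incompatible plans, so the pre-specified status of any subgroup result is undefined. This should be corrected.

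The covariate point is a recommendation that rests on the article's silence. It is not an error that the article commits. Its size is a 25% lower variance of a pairwise contrast at ρ = 0.5, and 35% to 15% over ρ from 0.3 to 0.7. It applies only if the analysis would otherwise be of unadjusted change. It concerns baseline ICIQ-SF alone, since the article gives nothing from which to quantify a gain from age or BMI. To say that the trial gives away a quarter of its variance would go beyond the document.

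**What to change.** 1. Replace the {20b} sentence with one fixed list: age (50 years), baseline ICIQ-SF (13) and BMI (25 kg/m²). Either add UI type to it now or remove UI type from the Discussion, and make the Discussion refer to this list.
2. State that each factor is examined by one arm-by-subgroup interaction test, labelled exploratory, with no confirmatory claim.
3. In {20a}, specify baseline ICIQ-SF (continuous) as a covariate in the primary GEE, with the post-baseline visits as outcomes and arm, visit and arm-by-visit as terms.

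The cost is analysis wording and a dated amendment, which should precede any comparison of outcomes by arm. No new data are needed: age, BMI and ICIQ-SF are already collected at baseline, and UI type is established at enrolment by the diagnostic questionnaire.
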